### ***Detection and management of adverse events***

An adverse event is defined as **any untoward medical occurrence in a trial participant who has been administered a pharmaceutical product.**

Serious adverse event is defined as a specific type of adverse event which result in the any of following:

- Death
- Life threatening
- Hospitalization, or causes prolonged hospitalization
- Significant disability or incapacity
- Causes congenital anomaly

All adverse and serious adverse events will be reported to the ethics committee by the principal investigator.

### ***Quality control***

All the doctors, nurses and pharmacists participating in the study will be trained on the specific neurologic examination required for patients. The investigator will be the overseer of the site

During each visit, data collected on the questionnaires will be checked for completion and verified. Information of the patients will be verified at each visit to ensure that it remains current. All the information for the trial will be locked up at the Wits Palliative care offices. Required files for a specific day will be retrieved for use on the specific day, and returned to the main office.

### ***Data collection, management and analysis***

All patients will be allocated a unique identifier that will also serve as their file number on site. All the information for the patient, laboratory results, and questionnaires from different visits, together with the signed informed consent will be kept in the patient's file. The files will be locked up in a cupboard with limited access control.

Double entry of data collected will be entered using Microsoft Access. R statistical package will be used to analyse the data. Descriptive statistics will be used to describe the demographics and clinical characteristics of the population studied.

The primary outcome (pain relief between baseline and end of the study) will be compared for the

- significance of overall pain relief for repeated measures using univariate analysis of variance (ANOVA)
- Association of the drug and the level of pain relief between different subjects using ANOVA.

The number needed to treat (NNT) will be calculated to assess the effectiveness of the drugs, while the number needed to get severe side effects will be calculated as NNF. During analysis subjects will be adjusted according to exposure to neurotoxic drugs. Analysis will also be done using the intention to treat analysis, where all randomised subjects will be included in the analysis to reduce bias.

The number treated analysis will also be done looking only at those subjects who managed to reach the maximum dose of the drugs. This however is subject to selection bias as subjects who developed side effects and those who were lost to follow up will be excluded. The effect of the use of other pain medication in together with the intervention being tested will also be analysed.

The results will be adjusted for ART during analysis, as all patients including those already on ART will be included in the study.

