## Study Summary

**Study purpose:** to assess the effectiveness of Amitriptyline compared to placebo in the management of moderate to severe HIV- related peripheral neuropathy in a population using ARV and not using ARV therapy

**Study design:** A double blind randomised controlled trial using a cross over design

**Sample Size:** 124 participants; 62 on ARV therapy and 62 not on ARV therapy followed up for a total of 15 weeks

**Study population:** adult men and women with documented HIV infection and moderate to severe HIV related distal sensory neuropathy

Visit schedule: An information session with recruitment, followed by a screening visit and an enrolment visit. After enrolment there will be five scheduled visits and weekly telephonic follow-up if written consent provided for that. Optional visits to the Palliative care centres may be done at any time during office hours for concerns, advice or further information. After hours telephonic contact will be available.

Study duration: the total duration of the study is 14 months. Three months for start up, training and preparation, enrolment closes after 6 months; the last participant exiting at month 11, and three months analysis and write up.

Primary objective: A measurement of the difference in pain intensity at the beginning and end of each 6 week treatment period.

Secondary objective: These will be adverse side effects of treatment, minimum effective doses, maximal tolerated doses, mood and effect on activities of daily living.

Study sites: Participants will be recruited from the Nthabiseng HIV Clinic at the Chris Hani Baragwanath Hospital, the Helen Joseph Hospital HIV clinic, and the palliative care clinic and outreach services.

Regulatory and monitoring: The Medicines Control Council (MCC) approval is not required since the drug is being used for indicated purposes. The MCC will be notified. The trial will be registered with the SA National Trials Register, and the Cochrane trials register. Ethical approval will be sought from the Wits REC and regular progress reports submitted as well as SAE, AEs and protocol violations. A study DSMB will be constituted who will perform an interim analysis as well as monitor the trial for safety and protocol violations.

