### ***Cross over design***

A cross over design is proposed for the following reasons: HIV has a complex disease course, and it is acknowledged that there may be many different mechanisms for the DSN so it is desirable if the participant acts as their own control. It is considered that the disease course will not significantly deteriorate in the follow up period of 15 weeks, although the baseline pain intensity will be measured at the start of each treatment intervention. It is anticipated that the follow up period is not too long to see a significant attrition rate. There will be two sub-groups: those stable on ARV with DSN and those not on ARV drugs. Secondly, the disease process is fairly stable over the proposed 14 weeks and the survival times for most participants will be more than proposed trial period.

Washout period: The SAMF 8 cites a plasma  $t_{1/2}$  of 10-50 hours, but also notes that the nortriptyline metabolite is active. The rule of thumb would be 5 half-lives, but in this case, you'd need to track down the metabolite's elimination. (Handbook of Basic Pharmacokinetics including Clinical Applications (6th edition). Ritschel WA and Kearns GL. APHA, Washington, 2004) gives a  $t_{1/2}$  for nortriptyline of 14-90 hours. On that basis, you'd be looking at a wash-out of at least 450 hours, or 18.75 days. Personal correspondence [name]

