### **Randomisation**

The randomisation allocation provided by the manufacturers of the placebo and active product. Participants will receive either regime A or regime B in a random manner. One regime will contain 6 weeks of active substance, followed by three weeks washout, then with 6 weeks of placebo, the other will contain 6 weeks of placebo followed by three weeks washout, then 6 weeks of active substance. Patients will be randomly allocated via a concealed allocation; the randomisation will be generated by block randomisation methods.

[figure not shown]

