### **Side effects**

Side effects will be continually monitored throughout the study as part of symptom control. (Appendix IV)

| Amitriptyline |
|----------------------|
| Dry mouth            |
| Sedation             |
| Weight gain          |
| Confusion            |
| Dizziness            |
| Palpitations         |
| Constipation         |

|       |
|-------|
| Other |
|-------|

Patients who develop side effects will be assessed by a doctor. Patients assessed as having serious adverse events will be withdrawn from the study, and reasons recorded. The total period of the study will be 6 weeks from enrolment. After being enrolled, subjects will be monitored for pain relief, symptom control and quality of life by the nurse, after which an intervention will be put in place. Monitoring will be done weekly by a professional nurse. Intervention can be one of the following:

- Increase the dose, and continue with the trial
- Maintain the dose, and continue with the trial
- Stop the drug because of adverse events, and drop from the study

For those that have been found to be not effective, alternative treatment will be offered.

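### The analysis section measures the primary outcome from baseline to end of study, contradicting the per-period objective, and states no within-patient comparison of amitriptyline with placebo

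*Protocol*

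**What the plan says.** - **Objective.** The Study Summary gives the primary objective as "A measurement of the difference in pain intensity at the beginning and end of each 6 week treatment period".
- **Design.** The Randomisation section describes two sequences. "One regime will contain 6 weeks of active substance, followed by three weeks washout, then with 6 weeks of placebo"; the other sequence reverses the order. The Cross over design section gives the reason: "it is desirable if the participant acts as their own control". It adds that "the baseline pain intensity will be measured at the start of each treatment intervention".
- **Analysis.** The Data collection, management and analysis section states: "The primary outcome (pain relief between baseline and end of the study) will be compared for the" two items. The first is "significance of overall pain relief for repeated measures using univariate analysis of variance (ANOVA". The second is "Association of the drug and the level of pain relief between different subjects using ANOVA".
- **End of study.** The visit schedule under Study procedures puts the exit visit at week 15. The Side effects section says instead: "The total period of the study will be 6 weeks from enrolment".
- **Second analysis section.** The later section on data collection, management and analysis says only that the analysis is by intention to treat and that the biostatistician will test the outcomes. It does not restate the primary outcome or name a contrast.

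**The concern.** A two-period cross-over answers its question by comparing each patient's response on drug with the same patient's response on placebo. The objective and the design rationale point that way; the analysis section does not. Measured from first baseline to week 15, the outcome spans both treatments and the washout, so it is not the quantity named in the objective.

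The choice affects the conclusion. An analyst following this section could report a before-after test, a comparison of the two sequences in their last period, or per-period changes, and these can disagree. The Protocol itself notes that the placebo effect in pain studies is well documented and that two earlier amitriptyline trials were negative. A significant result for overall pain relief could then be misread as efficacy.

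**Working it through.** **Inputs from the Protocol.** Difference of 2 on a 0-10 scale, SD read as 2, 90% power, alpha 0.05, 46 participants required, loss about 10%, enrolment 124.

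**Assumptions.** Two-sided alpha; 1:1 allocation to sequences; 124 × 0.9 ≈ 112 completers, 56 per sequence; score SD σ = 2; one common correlation ρ = 0.5 between any two scores of a patient; no carry-over unless stated. The Protocol gives no correlation and no figure for the placebo response.

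**The stated 46.** A two-sample t-test with difference 2 and SD 2 needs 22.02, so 23 per arm and 46 in total, which matches. A paired test with SD of the within-patient difference equal to 4 gives 44. The match therefore does not show which calculation was used.

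**What baseline to week 15 measures.** Assume a placebo response of 1 point.
- Drug effect 0: the fall is 1 in both sequences.
- Drug effect 2: the fall is 1 in those ending on placebo and 3 in those ending on drug, 2 on average.

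The overall mean is above zero even when the drug does nothing.

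**Test 1, overall pain relief, read as before-after.**
- SD of change = √(2σ²(1−ρ)) = √(2 × 4 × 0.5) = 2. SE = 2/√112 = 0.189.
- Common fall of 1 point: z = 1/0.189 = 5.3; significant in over 99% of trials with no drug effect.
- Fall of 0.5: z = 2.65; about 75%. Fall of 0.25: z = 1.32; about 26%.
- With 46 patients and a fall of 1 point: about 91%.

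**Test 2, between different subjects, read as sequences compared at week 15.**
- SE = 2 × √(2/56) = 0.38.
- Within-patient contrast of per-period changes: variance = 4σ²(1−ρ)/112 = 8/112, SE 0.27.
- Within-patient contrast of end-of-period scores: variance = 2σ²(1−ρ)/112 = 4/112, SE 0.19.
- The variance for test 2 is 8σ²(1−ρ)/112 = 16/112. The ratios are 2 against changes and 4 against end scores, whatever the common ρ.

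**Power of test 2.**
- Difference of 2, 46 patients: 92% if the SD of change is 2, 67% if it is 2.83. At 112: over 99.9% and 96%.
- Difference of 1, 112 patients, ρ = 0.5: about 75%, against 96% for within-patient changes and over 99.9% for within-patient end scores.

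**Is 46 still enough for a within-patient contrast?** For a difference of 2, power at 46 is over 99.9%, 99.7% and 91% when the SD of the within-patient difference is 2, 2.83 and 4. No larger sample is needed over this range.

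**Change scores or end scores.** Let scores within one period correlate at w, and keep 0.5 across periods. The variance ratio of change to end-score contrast is 4σ²(1−w)/(2σ² × 0.5) = 4(1−w). This is 2 at w = 0.5, 1.0 at w = 0.75 and 0.8 at w = 0.8.

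**Day-63 baseline.** Suppose no drug effect at the end of either period, but 1 point of relief persisting to day 63 in those who had drug first. Subtracting baselines gives drug minus placebo of −1 in that sequence and 0 in the other, an average of −0.5 that falsely favours drug. Entering the baseline with coefficient b gives −0.5b.

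**The case against.** The bullets are terse. The first mentions repeated measures and lists no model terms; read with the objective and the own-control rationale, treatment could be the repeated factor. The second, without carry-over, is a randomised comparison of drug with placebo, and at the planned enrolment it has ample power for a 2-point difference. Period terms and the handling of incomplete periods are commonly left to a statistical analysis plan, which is not at hand.

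Much of this stands, and it rules out several stronger inferences that a reader might draw:

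- *That the plan cannot estimate amitriptyline against placebo.* Not supported. The second test can, inefficiently, from period 2 alone. If the study is taken to end at 6 weeks, it becomes a parallel comparison in period 1.
- *That the fourfold variance is the like-for-like loss.* It sets changes against end scores. On the Study Summary's change measure the ratio is about 2.
- *That subtracting baselines doubles the variance.* This follows only from assuming one common correlation; at w = 0.75 there is no penalty.
- *That repeated-measures ANOVA drops incomplete patients and so breaks intention to treat.* This depends on implementation; no complete-case rule is stated.
- *That the text was taken from another study.* The 6-week statement, and the reference to an open study under Limitation of the study, fit a different design, but the document does not show their origin.

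What the objection does not remove is the conflict over the primary outcome. The Protocol fixes it in two incompatible ways, and a later plan consistent with the analysis section would inherit the wrong one.

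**Conclusion.** The point holds as an internal contradiction with consequences for inference. The analysis section's primary outcome, baseline to week 15, is not the per-period outcome of the Study Summary, and neither listed test states the within-patient contrast for which the cross-over was chosen. The contradiction and the missing contrast rest on the wording alone.

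The sizes rest on assumptions. The false-positive rate of the before-after reading runs from about 26% to over 99% as the assumed common fall goes from 0.25 to 1 point, with SD of change 2 and 112 completers. The precision loss of the second test is 2 times in variance against per-period changes and 4 times against end scores, under a common correlation and no carry-over. At full enrolment that loss matters little for a 2-point effect and more for a smaller one.

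**What to change.** In the Data collection, management and analysis section, replace the parenthesis and both ANOVA bullets with:

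- **Outcome:** pain intensity (0-10) at the start and end of each 6-week treatment period, as in the Study Summary.
- **Primary contrast:** amitriptyline minus placebo within patient, from a model in R with treatment, period, sequence and ARV stratum as fixed effects and patient as a random effect.
- **Analysis set:** all randomised patients with at least one period outcome. Say openly that this is slightly narrower than the present statement that all randomised subjects are included.
- **Baselines:** state in advance how the period baselines enter. The day-63 score is taken after randomisation and can carry residual drug effect. If it is subtracted or used as a covariate, add a sensitivity analysis of end-of-period scores without it.

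Reconcile the 6-week study length under Side effects with the 15-week cross-over.

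The cost is small: protocol wording only. The measurements are already scheduled, R is already named, adjustment for ART is already planned, and no added participants are needed over the range of SDs checked.

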## Trial abstract

A double blind randomised controlled trial to assess the effectiveness of amitriptyline compared to placebo in the management of moderate to severe HIV- related peripheral neuropathy. A cross over design will be used and 124 adult male and female volunteer participants with moderate to severe HIV related neuropathic pain will be followed up for a total of 15 weeks. Sixty two participants will be clinically and virologically stable on ARV drugs and 62 will not be in ARV therapy or intending to start in the next four months. In the first six weeks participants will be given either amitriptyline or identical looking placebo titrated to either effect or a maximum dose of 150mg. Then following a three week 'washout' period, participants will be 'crossed-over' to the other arm and titrated to either effect or a maximum dose for 6 weeks. Pain intensity will be measured on a daily basis and recorded into a pain diary by the participant and regular telephonic contact will be maintained between the study nurse and the participants. Pain intensity using tools validated for neuropathic pain, as well as other data will be collected at face to face interviews at each of the 5 scheduled follow up visit. Data collected will include information on adverse events, physical functioning and quality of life.

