## **METHODS**

### **Sample size calculations**

These have been calculated by a statistician, in the Wits School of Public Health.

The sample size will be determined with the following variables considered:

90% power,  $\alpha=0.05$ , effect is difference of 2 on a 0-10 scale; variance is 2SD. Variability of the distribution of the population was estimated from existing local clinical data and from previous estimates in the literature. The size of the placebo effect was estimated after considering the literature. For a cross-over design 46 participants will be required. Assuming two distinct sub-populations, those stable on ARV therapy and those not on ARV therapy and a loss to follow-up of ~10%.

**Enrolment target is 124 participants:** 62 on ARV therapy and 62 not on ARV therapy

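### The primary ANOVA has no within-participant treatment contrast, period term or period-level error term; if several visit scores share one pooled residual, the nominal 5% treatment test can reject about 8% to 18% under a true null

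*Protocol*

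**What the plan says.** The Protocol section on data collection, management and analysis defines the primary outcome as pain relief from baseline to the end of the study and gives two tests. The first is "significance of overall pain relief for repeated measures using univariate analysis of variance (ANOVA"). The second relates drug to level of pain relief across different subjects, again by ANOVA. Neither says which scores enter or which error term is used.

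Three other places bear on this:

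- **Allocation (Randomisation).** "One regime will contain 6 weeks of active substance, followed by three weeks washout, then with 6 weeks of placebo"; the other regime reverses the order. Treatment is therefore assigned once per period, so each participant supplies two treatment units.
- **Scores (Trial abstract, and the follow-up table in Study procedures).** Pain intensity "will be collected at face to face interviews at each of the 5 scheduled follow up visit". The table puts these visits at weeks 3, 6, 9, 12 and 15. With enrolment there are six site scores, three per period. Weeks 3, 6, 12 and 15 are on treatment. Enrolment and week 9 are the starts of the two periods.
- **Primary objective (Study Summary).** The quantity of interest is the change in pain from the start to the end of each treatment period, which is one value per participant per period.

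The error rate to be held is stated under Sample size calculations: "90% power, $\alpha=0.05$ , effect is difference of 2 on a 0-10 scale".

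**The concern.** The Protocol justifies the crossover by having each participant serve as their own control. The drug effect should therefore be a within-participant contrast between two periods, judged against the variation of that contrast between participants. The first ANOVA item names no such contrast, and the second is a between-subject comparison.

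A univariate repeated-measures F test over several visits is exact only if all differences between visits have the same variance (sphericity). Equal variances with equal correlations are sufficient for that, but not necessary. Visits nested in two periods and spaced over 15 weeks would not normally meet the condition, because scores in the same period tend to be more alike than scores in different periods. If treatment is then tested against a single pooled within-subject residual, the two on-treatment scores in a period are treated as independent evidence on a treatment that was allocated once.

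At stake is the 5% error rate. The trial is meant to support or refute existing evidence after two amitriptyline trials that showed no effect, so a false positive would matter.

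**Working it through.** **Inputs from the Protocol.** Alpha 0.05 (two-sided assumed), power 90%, difference 2 points, SD 2 (my reading of "effect is difference of 2 on a 0-10 scale; variance is 2SD"), 46 required, 124 enrolled, about 10% loss, two periods, visits as listed above. **Not given:** any correlation between pain scores, so a range is assumed.

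**The plan's own figure.** A two-sample t test with difference 2, SD 2, two-sided 0.05 and 90% power needs 23 per group, or 46 in all, which matches "For a cross-over design 46 participants will be required". The normal approximation is 2 × (1.960 + 1.282)² × 2²/2² = 21.0, so 22 per group. This reproduces the stated number but gives no within-participant correlation. The Protocol states no error rate for the ANOVA other than the nominal 0.05.

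**Closed form.** Take unit variance, m scores per period, correlation w within a period and b between periods.

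- True variance of the difference between a participant's two period means: (2/m) × [1 + (m − 1)w − mb].
- Variance implied by a pooled within-subject residual: (2/m) × (1 − r̄), where r̄ = [(m − 1)w + mb]/(2m − 1).
- Ratio R = [1 + (m − 1)w − mb]/(1 − r̄). Actual size of the nominal 5% test ≈ 2 × [1 − Φ(1.96/√R)].

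With m = 2 (weeks 3 and 6; weeks 12 and 15):

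| w / b (assumed) | 1 + w − 2b | 1 − r̄ | R | √R | Size, formula | Size, simulated (n = 46; 112) |
|---|---|---|---|---|---|---|
| 0.5 / 0.5 | 0.500 | 0.500 | 1.00 | 1.00 | 5.0% | 4.9%; 5.0% |
| 0.6 / 0.5 | 0.600 | 0.467 | 1.29 | 1.13 | 8.4% | 8.4%; 8.4% |
| 0.6 / 0.4 | 0.800 | 0.533 | 1.50 | 1.22 | 11.0% | 11.4%; 10.8% |
| 0.7 / 0.4 | 0.900 | 0.500 | 1.80 | 1.34 | 14.4% | 14.6%; 14.0% |
| 0.8 / 0.5 | 0.800 | 0.400 | 2.00 | 1.41 | 16.6% | 17.0%; 17.3% |
| 0.8 / 0.4 | 1.000 | 0.467 | 2.14 | 1.46 | 18.1% | 17.4%; 18.0% |

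The simulations had no true effect, used 4,000 runs per cell (standard error about 0.3 percentage points at 5%), and took n = 46 (the stated requirement) and n = 112 (124 × 0.9 = 111.6). Correlation decaying with time, at 0.5, 0.7 and 0.9 per 3 weeks, gave 12.0% to 17.8% for the same test.

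**With one value per period,** m = 1 and R = (1 − b)/(1 − b) = 1 for any b, so the size is 5%. Simulated sizes were 4.5% to 5.6% for one change score per period and 4.6% to 5.8% for the end-of-period score. Testing treatment on period means, in its own period-level error stratum, gave 4.5% to 5.3%.

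**Other readings of the same wording,** all under unequal correlations:

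- All six scores with one pooled residual, the two period baselines counted as on treatment: 11% to 28%.
- An overall test of differences among the six visits: 5% to 9%. This tests time, not drug.
- The treatment difference in start-to-end change, judged against a pooled residual: 0.3% to 3.6% with nested periods, and 3% to 7% with decaying correlation. Here the error is mostly in the conservative direction.

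**The case against.** The strongest objection is that the Protocol never says all visit scores form the repeated factor. Its analysis section defines a change between two time points, and the Study Summary defines one change per period. With one value per period the factor has two levels, sphericity holds trivially and the size is 5%. Moreover, a univariate ANOVA need not be uncorrected or use a single residual. R, which the Protocol names, fits separate error strata, and such detail is commonly left to a statistical analysis plan, which is not at hand.

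Much of this stands. A reader might infer that the planned test is known to exceed 5%, or that its standard errors must be too small. The documents support neither: they give no correlations, no choice of visits and no error term, and one reading errs the other way. Nor should the 5% to 9% for the overall visit test be read as a false-positive rate for amitriptyline, since it does not test the drug. The missing sphericity correction is not in itself a finding.

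What does not stand is that the wording secures the safe reading. The stated outcome runs from baseline to the end of the study and so spans both treatments. The first item calls for repeated measures without a treatment contrast, and the second compares different subjects. An analysis plan that followed these sentences would not be led to the per-period comparison in the Study Summary. The point therefore concerns the method the Protocol states, not detail it omits.

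**Conclusion.** The point holds as a conditional one. The stated primary analysis lacks the within-participant treatment contrast, period term and period-level error term that a two-period crossover needs, and it permits an analysis that does not hold the nominal 5%. If the four on-treatment scores enter with one pooled residual, the treatment test rejects a true null about 8% to 18% of the time. That range rests on assumed correlations (0.6 to 0.8 within and 0.4 to 0.5 between periods, or 0.5 to 0.9 per 3 weeks decaying) and on that choice of visits and residual. With one value per participant per period, or with equal correlation throughout, the size is about 5% and the problem does not arise. It should be corrected, because the remedy is cheap and the primary objective already points to it.

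**What to change.** In the Protocol section on data collection, management and analysis, replace the first ANOVA item with one of the following:

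1. A within-participant comparison of amitriptyline and placebo on one pain value per treatment period, namely the change from the start to the end of that period as in the Study Summary objective, with period in the model.
2. A linear mixed model on the visit scores, with treatment, period and visit as fixed effects and participant and participant-by-period as random effects. The enrolment and week 9 scores should be handled as period baselines, not coded as on-treatment responses.

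The cost is one sentence of rewording and routine R code, with no extra data or participants. Confidence intervals will be wider than those from a pooled residual. For the mean of two on-treatment scores, the √R column implies 13% to 46% wider under the nested correlations assumed. That corrects an understated standard error and is not a loss of information.

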## **DATA COLLECTION MANAGEMENT AND ANALYSIS**

Data will be entered in real time by a data capturer into a Microsoft Access database. 20% of random sample of data will be double entered by a second data enterer and checked for error rate. The double entry will be adjusted according to the error rate. Hard copy of the

consent forms will be kept in a separate locked filing cabinet. Hard copy of the data forms will be kept in another filing cabinet. After closure of the study, forms will be archived and stored for 7 years. Analysis will be in an intention to treat basis. Primary and secondary outcome measures will be calculated and tested for statistical significance by the biostatistician.

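### The named primary ANOVA, read as the within-participant comparison, uses only participants with both periods; this does not fit the promised analysis of all randomised, and can bias the effect modestly if loss differs between sequences

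*Protocol*

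**What the plan says.** The protocol subsection *Data collection, management and analysis* (after *Quality control*) lists two analyses of the primary outcome. The first is "significance of overall pain relief for repeated measures using univariate analysis of variance (ANOVA". The second is "Association of the drug and the level of pain relief between different subjects using ANOVA". The same subsection adds: "Analysis will also be done using the intention to treat analysis, where all randomised subjects will be included in the analysis to reduce bias". The later main section *DATA COLLECTION MANAGEMENT AND ANALYSIS* makes this the general rule: "Analysis will be in an intention to treat basis".

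*Sample size calculations* allows for "a loss to follow-up of ~10" per cent. *Randomisation* describes two sequences of two six-week periods with a washout between them.

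Two places foresee participants leaving for reasons tied to treatment or pain. *Side effects* has participants leave the study when the drug is stopped for adverse events. The ethics discussion of placebo has them leave when amitriptyline is the only workable option for their pain.

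The protocol does not say how a participant with only period 1 enters either ANOVA. It also describes the primary outcome in two ways. *Study Summary* has "A measurement of the difference in pain intensity at the beginning and end of each 6 week treatment period", while the analysis subsection takes the change from baseline to the end of the study.

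**The concern.** A method and an analysis set are both fixed in the protocol, and they do not fit each other. In a two-period cross-over, classical repeated-measures ANOVA compares treatments within participants, so anyone lost after period 1 drops out of the comparison. A statistical analysis plan that followed the protocol faithfully would inherit the mismatch.

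The stake is bias. If participants with high pain leave more often, and more of them leave while on placebo, the pairs that remain show too little pain on placebo. The drug effect is then understated. The protocol recognises this kind of selection for its maximum-dose analysis, where it warns that excluding those with side effects or lost to follow-up causes bias. It gives no such warning for the primary ANOVA. The trial is meant to confirm or overturn two earlier trials that found no effect, so a pull towards no effect matters.

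**Working it through.** **Inputs from the protocol.** Difference 2 on a 0–10 scale; spread read as SD 2; α 0.05 (taken as two-sided); power 90%; 46 participants for a cross-over; about 10% loss; target 124 (62 per ARV stratum).

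**Assumptions not in the protocol.** Within-participant correlation ρ of 0.3 to 0.7; approximately normal scores; no carry-over; loss after period 1 logistic in period 1 pain, with slope 0.75 per point (1.5 per SD); 25% loss as a worse case; every leaver has a period 1 score.

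**1. The plan's own figure.** With difference 2 and SD 2, a two-group t-test has power 0.8997 with 22 per group and 0.9125 with 23 per group. So 46 in total is reproduced, which supports reading the spread as SD 2. (That it comes from a two-group formula is a separate matter.)

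**2. Numbers left.** 124 × 0.9 = 111.6 and 62 × 0.9 = 55.8. Both exceed 46, so power is not the issue.

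**3. Why one-period participants add nothing.** The model is score = participant + period + treatment + error. A participant with a single score is fitted exactly by their own participant term. Let d be period 1 minus period 2 pain among complete pairs. The period-adjusted effect is

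effect = (mean d in placebo-first − mean d in amitriptyline-first) / 2.

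Fitting the ANOVA with participant terms to all rows, and then to complete pairs only, gave identical treatment estimates.

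**4. Bias formula.** Let m be the amount by which stayers' mean period 1 pain lies below that of everyone who started, written m_P in placebo-first and m_A in amitriptyline-first. Stayers' period 2 mean falls by ρm, so their mean d falls by (1 − ρ)m. Hence

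bias = −(1 − ρ)(m_P − m_A) / 2.

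**5. Results.** True effect 2, simulated with 1,000,000 participants per sequence:

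| Who leaves | Overall loss | Loss, amitriptyline-first / placebo-first | m_A | m_P | Estimate at ρ = 0.3 / 0.5 / 0.7 |
|---|---|---|---|---|---|
| one rule, both sequences | 10% | 5% / 15% | 0.13 | 0.35 | 1.92 / 1.94 / 1.97 |
| one rule, both sequences | 25% | 15% / 35% | 0.36 | 0.76 | 1.86 / 1.90 / 1.94 |
| placebo-first only | 10% | 0% / 20% | 0 | 0.45 | 1.84 / 1.89 / 1.93 |
| placebo-first only | 25% | 0% / 50% | 0 | 1.06 | 1.63 / 1.73 / 1.84 |

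Checks by hand:
- Row 1, ρ = 0.7: 0.3 × (0.353 − 0.129) / 2 = 0.03.
- Row 3, ρ = 0.3: 0.7 × 0.45 / 2 = 0.16.
- Row 2, ρ = 0.7: 0.3 × (0.758 − 0.356) / 2 = 0.06.
- Row 4, ρ = 0.3: 0.7 × 1.06 / 2 = 0.37.

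**6. When the bias vanishes or reverses.** With a true effect of 0 and one common rule, m_P = m_A and the bias is 0.00. With loss in placebo-first only, the row 3 bias is the same when the true effect is 0, because m_P does not depend on the effect. If the same pain-related loss occurs in amitriptyline-first only, m_P = 0 and m_A = 0.45 at 10% loss. The sign then flips, giving 2 + 0.3 × 0.45 / 2 = 2.07 to 2 + 0.7 × 0.45 / 2 = 2.16.

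**7. Other loss shapes, one common rule.** Slopes of 0.5 to 1 per point, or a hard pain cut-off, give 0.02 to 0.18 at 10% loss. At 25.8% loss (1 − 46/62, the loss that would take a stratum down to 46) they give 0.04 to 0.31. With a true effect of 1 and 10% loss the range is 0.01 to 0.10.

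**8. The alternative.** A likelihood fit of all observed periods, with treatment and period fixed and participants correlated, returned 2.00 in every row of the table.

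**The case against.** The protocol nowhere limits the ANOVA to participants with both periods; that is a property of the classical method. The intention-to-treat analysis is announced as a further analysis with no model named. The second, between-participant ANOVA could use period 1 from everyone who has an outcome, and a statistical analysis plan not at hand could specify imputation. A reader might therefore infer that the plan cannot include all randomised participants at all. The documents do not support that. What stands is narrower: the named within-participant method does not do so, and the protocol provides no bridge.

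A reader might also infer that any loss related to period 1 pain biases the result. It does not. The selection must differ between sequences, and step 6 shows it cancels otherwise.

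The repeated factor is not named and could be visits, and the primary outcome is defined in two ways. This stands too. The point holds for the within-participant treatment reading, and the outcome must be settled first.

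Finally, a mixed model cannot use a participant with no outcome at all. Both removal routes can act during period 1, before the week 6 score. For those participants the change of model alone gains nothing, so the fix needs an explicit rule.

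**Conclusion.** The mismatch is real and worth correcting. Read as the within-participant comparison, the named ANOVA leaves out the roughly 10% whom the protocol expects to lose, while the protocol promises an analysis "where all randomised subjects will be included in the analysis to reduce bias".

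The consequence is modest at the planned loss: 0.03 to 0.16 points of a 2-point effect (about 2% to 8%). At 25% loss it is 0.06 to 0.37 points (3% to about 18%). In the tabulated scenarios the direction is towards no effect, but it could reverse if pain-related losses fall mainly on amitriptyline. These sizes rest on the assumed correlation, shape of loss and SD of 2, and on leavers having a period 1 score. Differential loss is foreseeable from the protocol's own removal routes, but its extent is not known.

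**What to change.** First reconcile *Study Summary* and the analysis subsection on what the per-period pain outcome is. Then, in *Data collection, management and analysis*:

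- Replace the univariate ANOVA by a linear mixed model fitted by restricted maximum likelihood to that per-period outcome. Use treatment and period as fixed effects, the adjustments for ART and neurotoxic-drug exposure that the protocol already promises, and participant as a random effect.
- Include every randomised participant with at least one post-randomisation period outcome.
- State how participants with no end-of-period score are handled, for example by using the week 3 and week 12 visit scores or the diary scores already collected.
- State that the model assumes loss depends only on observed data.
- Keep the complete-pairs ANOVA as a sensitivity analysis.

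The cost is wording in the protocol or the statistical analysis plan. No new data or visits are needed, and the model can be fitted in R, which the protocol already names.
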